### Procedure

A time schedule of enrollment, assessment visits, and VR-trainings for participants is shown in Fig. 3. During the first laboratory session (baseline; approximately 150 min), participants give informed consent, take part in a short psychoeducational group counselling and receive a self-help book to aid smoking cessation. Individuals are then asked to download the cigarette-tracking app and are instructed to log each smoked cigarette for the duration of their participation in the study. Thereafter, participants complete the cognitive bias assessments, questionnaire measures, and the carbon monoxide breath test. VR-based approach bias assessment takes place prior to the first training session and following the last training session. In total, smokers complete six sessions of VR-training (VR-avoidance or VR-placebo training) within 2 weeks. After completion of the final training session (post-test) and at a 7-week follow-up, participants are once again invited to complete cognitive bias assessment tasks, questionnaire measures, and the CO breath test and are asked to evaluate the training and indicate their awareness about training contingencies. Cigarette craving is measured at pretest, post-test, and follow-up, as well as after each training session, resulting in nine measurement points.

**Fig. 3 Fig3:**
[figure not shown]
Schedule of enrollment, assessments and interventions

### Data preparation and planned analyses

So that missing data can be filled in, multiple imputation and the modified Intention-To-Treat (ITT) principles [36] will be used. Prior to computation of the cognitive bias scores, error trials will be excluded from further analyses. Median reaction times will be used to minimize the influence of outliers.

To test for changes in cognitive biases, mixed design ANOVAs will be calculated. Due to random assignment to the experimental or to the placebo group, we expect a priori group differences to be small. Possible chance baseline imbalance between treatment arms will be taken into account by means of follow-up simple effects analyses. For approach biases, a 2 (condition: VR-avoidance training vs. VR-placebo training) × 2 (item content: smoking vs. control items) × 3 (time: pretest, post-test, follow-up) mixed design ANOVA will be conducted. For attentional and association biases, two separate 2 (condition) × 3 (time) mixed design ANOVAs will be calculated.

To evaluate the effects of training on self-reported average daily nicotine consumption, a 2 × 3 mixed ANOVA will be carried out in which the training condition is a between-subjects factor and time (pretest, post-test, follow-up) is a within-subjects factor.

Multilevel modeling (MLM) will be used to estimate the growth curve for nicotine consumption as measured with the cigarette-training app and craving ratings over time.

To explore whether the VR-training leads to increased abstinence rates, a Chi-square test will be computed.

To test the effect of training on other smoking-related variables (i.e., CO, FTND, smoking attitude, motivation to quit), a 2 (condition) × 3 (time) repeated measures MANOVA will be conducted. Significant multivariate effects will be followed up with separate ANOVAS on each dependent variable. In case of significant interactions, discriminant factor analyses will be conducted to identify possible associations between each of the dependent variables and group assignment.

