## Methods/Design

### Trial design

The present study is a randomized control trial comparing self-report, behavioral, and biochemical outcomes of the VR-AAT training to an active placebo control condition (Additional file 1). Smokers are randomly assigned either to the experimental (brief smoking cessation intervention, hereafter referred to TAU + VR-avoidance training) or to the sham-control condition (TAU + VR-placebo training). This study employs a 2 (condition: avoidance training vs. placebo training) × 3 (time: pretest/post-test: 3 weeks after baseline/follow-up: 7 weeks after baseline) mixed design. Because we expect the experimental condition to be more effective than the sham-training control condition, this protocol describes a superiority trial design. The training intervention occurs over the course of 2 weeks in which smokers complete six training sessions in total. Measures of cognitive biases (approach, attention, and association bias), self-report measures of smoking behavior and biochemically verified smoking intensity are applied at the pretest, post-intervention, and 7-week follow-up.

A priori power analyses were conducted using G*Power 3.1 (open-source software) [20]. Previous research on the efficacy of CBM trainings found a small to moderate effect size [12, 21]. We conducted a power analysis for a 2 × 3 mixed design ANOVA to detect a small-to-moderate effect (Cohen’s d = .30). Our results indicated that a total sample size of 74 is required to achieve 80% power at an alpha level of 0.05 and an assumed correlation of r = .50 between the repeated measures. Because we expect some attrition due to our multisession design, we decided to include 100 participants, which is 50 per condition.

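### The planned remedy for chance baseline imbalance, follow-up simple effects tests, does not condition on the pretest; the pretest should enter as a covariate

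*Protocol article*

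**What the plan says.** Under Data preparation and planned analyses, the protocol article tests changes in cognitive biases with mixed ANOVAs. Approach bias gets a condition × item content × time model; attentional and association bias each get a condition × time model. In all of them the pretest is one of three levels of the time factor. The paragraph expects small group differences at the start because of randomisation, and adds: "Possible chance baseline imbalance between treatment arms will be taken into account by means of follow-up simple effects analyses".

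Self-reported daily consumption is handled the same way: "time (pretest, post-test, follow-up) is a within-subjects factor". No pretest covariate is named for any outcome.

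The sample size in Trial design rests on "an assumed correlation of r = .50 between the repeated measures". It concludes that "a total sample size of 74 is required to achieve 80% power at an alpha level of 0.05", and then: "we decided to include 100 participants, which is 50 per condition". Randomization and blinding describes 1:1 allocation in permuted blocks of 50 with no further stratification, so pretest values are left to chance.

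**The concern.** The article commits to a named procedure for a named purpose, and the procedure does not serve it. Comparing the arms at post-test ignores the pretest. Comparing time points within an arm is not a treatment comparison. Neither conditions on where the two groups started.

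The main ANOVA does not fill the gap. Its condition × time interaction uses the pretest only through change from baseline. That over-corrects an imbalance, because groups that start apart by chance tend to regress towards each other. Should an imbalance occur, the interaction and the simple effect err in opposite directions, and the plan has no analysis that settles which to believe. Approach bias and consumption are primary outcomes, and the pretest that would settle it is already collected.

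**Working it through.** **Inputs.** From Trial design: d = .30, r = .50, α = 0.05, N = 74 required, N = 100 planned (50 per arm). Assumed here: equal variances (SD = 1), equal correlations between all visits, two-sided tests.

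**The plan's own figure.** For the within-between interaction, λ = f²·N·m/(1−r), with df 2 and 2(N−2). With f = d/2 = .15 and m = 3 visits, N = 74 gives λ = .0225 × 74 × 3/.50 = 9.99 and power 0.806; N = 72 gives 0.795. The stated 74 is reproduced.

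**Size of a chance imbalance.** The standard error of the pretest difference is √(2/50) = 0.20 SD. So P(|δ| ≥ 0.3) = P(|Z| ≥ 1.5) = 13%, and P(|δ| ≥ 0.4) = P(|Z| ≥ 2) = 4.6%.

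**Error given δ, no treatment effect.**
- Post-test simple effect: +rδ
- Change contrast: rδ − δ = −(1−r)δ
- ANCOVA: rδ − rδ = 0

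At r = .50 and δ = 0.3 these are +0.15, −0.15 and 0 SD. At δ = 0.4 they are +0.20, −0.20 and 0 SD.

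**Conditional type I error of the simple effect.** The test rejects beyond 1.96 × 0.20 = 0.392. Given δ, the estimate has mean rδ and SD √(1−r²) × 0.20 = 0.173.
- δ = 0.2: about 5%
- δ = 0.3: (0.392 − 0.15)/0.173 = 1.40, giving 8.2% over both tails
- δ = 0.4: (0.392 − 0.20)/0.173 = 1.11, giving 13.4%

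At r = .50 the change contrast has the same rates; ANCOVA stays at 5%. Averaged over randomisations, simulation (20,000 replicates per setting) gave 4.6% to 5.3% for every method.

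**Power, like with like** (noncentral t, d = .30 at the visit or visits tested, N = 100, r = .50):

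| Contrast | Variance factor | Power |
|---|---|---|
| One visit, simple effect | 1 | 32% |
| One visit, change: 2(1−r) | 1.00 | 32% |
| One visit, ANCOVA: 1−r² | 0.75 | 40% |
| Mean of two visits, change: (1+r)/2 + 1 − 2r | 0.75 | 40% |
| Mean of two visits, ANCOVA: (1+r)/2 − r² | 0.50 | 56% |

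The covariate cuts variance by 25% at one visit and by 33% for the two-visit mean against change.

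**Range over r, one visit** (r outside .50 is an assumption):

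| r | Simple effect | Change | ANCOVA |
|---|---|---|---|
| .2 | 32% | 22% | 33% |
| .5 | 32% | 32% | 40% |
| .8 | 32% | 65% | 70% |

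ANCOVA is never behind, but its lead over the simple effect nearly vanishes at low r, and its lead over change narrows at high r.

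**The case against.** The strongest reply is that randomisation already makes the comparison unbiased. That stands: the bias described here exists only given the imbalance that occurs. The simple effect's conditional type I error is about 2% at δ = 0 and passes 5% only beyond roughly 0.2 SD, which is about one trial in three. Chance imbalance is, however, exactly what the quoted sentence claims to deal with.

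A reader might credit the covariate with raising power from 32% (the planned 2-df interaction at d = .30, N = 100) to 56%. That is not supported. Going from 2 df to a single contrast on the two-visit mean, with no covariate, already gives 40%; the covariate supplies the step from 40% to 56%.

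A reader might also infer that the trial has only 32% power. That depends on how d = .30 is read. The protocol's 74 reproduces with f = .15. If the effect is equal at both later visits, equating λ gives d = √18 × .15 = .636, and the planned interaction then has 81% power at N = 74 and 91% at N = 100. Which reading is meant is a separate sample-size question.

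Averaging the two visits is not safe as a requirement. If d = .30 is present at post-test only, the averaged ANCOVA tests 0.15 SD and has 18% power, against 32% for the planned interaction. For the VR-AAT, Procedure places assessment before the first and after the last training session, whereas Cognitive bias assessment includes follow-up; there may be no second visit to average.

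Finally, r = .50 is a general planning value, not one for reaction-time difference scores, so the power gain is uncertain. The quoted sentence covers only the cognitive biases. The consumption ANOVA shares the structure, but the MANOVA outcomes, the growth curves and the abstinence test are different analyses.

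**Conclusion.** The concern holds in a limited form. The protocol names a procedure for baseline imbalance that does not adjust for baseline, and the condition × time interaction does not adjust for it correctly either. At r = .50 and 50 per arm, about 13% of trials would have an imbalance of 0.3 SD or more. At 0.3 SD the post-test simple effect is off by 0.15 SD, half the planning d = .30. An imbalance of 0.4 SD or more has about a 5% chance; at 0.4 SD the error is 0.20 SD and the conditional type I error about 13%.

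The power gain for the same contrast is moderate at r = .50 (8 percentage points at one visit, 16 for the two-visit mean against change). At one visit it is as little as 1 point over the simple effect at r = .2, and 5 points over change at r = .8. These figures assume equal variances and correlations across visits and a common linear slope on the pretest. The protocol does not support a claim that the planned analysis is biased on average or exceeds 5% type I error overall.

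**What to change.** Replace the simple-effects sentence by a rule along these lines: the treatment effect on each cognitive-bias score, and on self-reported average daily consumption, is estimated by ANCOVA or a linear mixed model of the post-baseline values, with condition, time and condition × time as factors and that outcome's own pretest as covariate. The condition contrast is reported at each post-baseline visit.

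For the AAT, use the smoking-minus-control bias score and its pretest. For the VR-AAT, use post-test only if it is not measured at follow-up; the two sections on its timing should be reconciled. A contrast averaging the two visits may be added but need not be. The analysis population is a separate matter and need not change here.

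The cost is a small change of analysis wording and one degree of freedom per model. No new data are needed.

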### Biochemical verification

Expired carbon monoxide (CO) will be assessed at baseline, post-training, and 7-week follow-up using a Carbon Monoxide Monitor (piCO™ Smokerlyzer®; Bedfont Scientific Ltd).

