### Outcome measures

Primary outcome measures are changes in approach bias, which are measured by the assessment versions of the joystick-AAT and the VR-AAT, reductions in nicotine consumption, and abstinence rates. Secondary outcome measures will be changes in other cognitive biases as measured by a visual dot-probe task and the IAT, motivation to stop smoking, other health-related behavior, expired CO, cigarette craving, and explicit attitudes toward smoking.

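### Expired CO, the only biochemical measure, has no planned arm comparison of its own except as follow-up to a significant four-variable MANOVA

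*Protocol article*

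**What the plan says.** Under Data preparation and planned analyses, the protocol article plans one joint test for "other smoking-related variables (i.e., CO, FTND, smoking attitude, motivation to quit), a 2 (condition) × 3 (time) repeated measures MANOVA will be conducted". The next sentence is "Significant multivariate effects will be followed up with separate ANOVAS on each dependent variable". The section names no other analysis of CO.

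CO is the sole measure under Biochemical verification: "Expired carbon monoxide (CO) will be assessed at baseline, post-training, and 7-week follow-up using a Carbon Monoxide Monitor". Outcome measures places it among the secondary outcomes, in a list that includes "motivation to stop smoking, other health-related behavior, expired CO, cigarette craving, and explicit attitudes toward smoking". Trial design presents the study as "comparing self-report, behavioral, and biochemical outcomes of the VR-AAT training to an active placebo control condition".

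Other outcomes are handled differently in the same section:
- Self-reported consumption, a primary outcome, has its own analysis: "To evaluate the effects of training on self-reported average daily nicotine consumption, a 2 × 3 mixed ANOVA will be carried out".
- Attentional and association bias, both secondary, each get a separate 2 × 3 ANOVA.
- Craving, also secondary, gets a multilevel model.
- Abstinence gets its own test: "To explore whether the VR-training leads to increased abstinence rates, a Chi-square test will be computed".

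None of these waits on an omnibus result.

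**The concern.** CO measures smoke exposure. The three variables tested with it are questionnaire scores for dependence, attitude and motivation. If training lowers smoking without moving those scores, the joint condition × time test spreads an effect carried by 2 degrees of freedom over 8, and it may miss significance. The stated sequence then never reaches the CO ANOVA.

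Two things are at stake. One is power for the one objective measure in a trial whose consumption data are self-logged or self-estimated. The other is that a CO-specific result becomes conditional on significance, so that readers might see a CO comparison only when the joint test succeeds.

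**Working it through.** **Inputs from the article (Trial design; Data preparation and planned analyses).** d = 0.30, alpha 0.05, 80% power, r = .50 between repeated measures, N = 74 required, 100 planned; four variables, three visits.

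**Assumptions, because the article gives no figures.** Correlation between the four variables: 0, .3 or .5. The effects on the other three variables and the change common to both arms are varied below.

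**1. The stated sample size.** For the condition × time test, λ = f²·N·m/(1 − r), with f = d/2 = 0.15 and m = 3.
- N = 74: λ = 0.0225 × 74 × 3/0.5 = 9.99 on 2 and 144 df, power 0.806. The stated 74 reproduces.
- N = 100: λ = 13.5, power 0.914.

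**2. The gate at that effect size.** The multivariate condition × time test covers 4 variables × 2 time contrasts = 8 contrasts, with an exact F on 8 and N − 9 df. If only CO responds and the variables are uncorrelated, λ is unchanged but is spread over 8 df. The gate then opens with probability 0.53 (N = 74) or 0.70 (N = 100). The simulated chance that the CO ANOVA would be significant while the gate is shut (8,000 runs per scenario) is:

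| Effect on the other three | N = 74 | N = 100 |
|---|---|---|
| None (correlation 0 / .3 / .5) | 0.30 / 0.23 / 0.11 | 0.22 / 0.14 / 0.05 |
| Half that on CO (range) | 0.08 to 0.30 | 0.03 to 0.22 |
| Equal to that on CO (range) | 0.00 to 0.11 | 0.00 to 0.05 |

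**3. A 0.50 SD arm difference in CO at both later visits.** With this step pattern f = (0.50/2) × √2/3 = 0.118. Then λ = 0.0139 × 100 × 3/0.5 = 8.33 at N = 100 (power 0.73) and 6.17 at N = 74 (power 0.59). Simulated results with an effect on CO only and the interaction as the gate (ranges are over repeated runs):

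| | CO tested alone | Reached and significant, correlation 0 / .3 / .5 |
|---|---|---|
| N = 100 | 72–74% | 43–45% / 49–51% / 59–61% |
| N = 74 | 58–59% | 29–30% / 34% / 41–43% |

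**4. If the other variables also respond (N = 100, interaction gate).**
- 0.25 SD on each of the other three: 62% / 46% / 44%, against about 73% alone.
- 0.50 SD on all four: 74% against 74% at correlation 0, 67% against 72% at .3, 59% against 72% at .5.

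**5. If a significant multivariate time effect also opens the gate (effect on CO only).**
- No change in the placebo arm, N = 100: 55–69%.
- A further 0.30 SD fall in CO common to both arms: the time test is significant in 97–100% of runs. CO is reached and significant in 73% / 73% / 72% at N = 100, the same as ungated, and in 56% / 58% / 60% at N = 74 against 57% / 58% / 60% ungated.

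**6. CO at follow-up adjusted for pretest CO, no gate.** The residual SD is √(1 − 0.5²) = 0.866, so the standardised effect is 0.50/0.866 = 0.577. Noncentrality is 0.577 × √(100/4) = 2.89 at N = 100 and 0.577 × √(74/4) = 2.48 at N = 74. Power is about 81% and 69%; simulation gave 80–82% and 68–69%.

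**The case against.** The strongest objection is that the interaction-only gate is narrower than the text. The follow-up sentence refers to multivariate effects in general, and the sentence after it singles out interactions for a further analysis. Read literally, a significant time effect also leads to the CO ANOVA. All participants want to quit, and both arms receive the workshop, the self-help book and self-monitoring, so a time effect is likely. This stands: on that reading, with a common fall in CO, the loss disappears (step 5).

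The largest losses also assume a particular pattern, such as no effect at all on dependence, attitude and motivation. This stands in part. The loss is nil or small when all four respond equally and correlate at 0 to .3, but it is 13 points at .5 (72% to 59%), and half-size effects on the other three can leave it as large as in the CO-only case.

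An omnibus test followed by univariate tests is a recognised way to limit false positives among secondary outcomes, and CO is secondary. That is fair, but this protocol does not apply the device to its other secondary bias measures or to craving.

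Three stronger readings are tempting and are not supported:
- A reader might infer that CO is not compared between arms at all unless the gate opens. CO is part of the MANOVA's joint between-arm test; what may be missing is the comparison specific to CO.
- A reader might infer that abstinence rests on self-report alone. The article does not say how abstinence is defined, and it has a section headed Biochemical verification.
- A reader might infer that CO results would be withheld. Nothing bars descriptive reporting by arm, and a condensed article may leave that to the full plan.

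**Conclusion.** The point holds as a design weakness in a stated rule; it is not an arithmetic error. The only CO-specific arm comparison in the article is a follow-up to significant multivariate effects.

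The size of the loss is conditional. It is 12 to 30 percentage points at N = 100 (73 − 61 to 73 − 43) if the interaction is the gate and CO is the main variable to move. It is about nil if a time effect counts and both arms improve. These figures rest on r = .50 over time, which is the article's own value, and on assumed correlations between variables and assumed effect patterns. They do not show that the trial will lose its CO result.

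Two arguments for change do not depend on how the gate is read. A pretest-adjusted, ungated comparison has more power than the CO ANOVA even when that ANOVA is always run (about 81% against 73% at N = 100; 68–69% against 58–59% at N = 74). It also makes reporting of the one biochemical measure independent of significance. The change is worth making, but its importance is moderate because CO is secondary.

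**What to change.** Under Data preparation and planned analyses, take CO out of the MANOVA. State that the arm difference in CO at post-test and at follow-up will always be reported with a 95% CI, adjusted for pretest CO, whatever the other tests show. Label it secondary and supportive. Keep the MANOVA for FTND, attitude and motivation, and say which multivariate effect (condition × time, or any) triggers its follow-up ANOVAs.

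The cost is wording only: CO is already measured at all three visits. The downside is that one secondary test leaves the omnibus gate, which is why the supportive label is needed.

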## Discussion

The aim of the present study is to explore whether a newly developed VR-training is capable of modifying cognitive biases and/or reducing smoking in terms of nicotine consumption or withdrawal over and above a sham-training control condition. Therefore, we describe a randomized, multisession placebo-control design to explore the efficacy of a VR-based AAT-training in a group of regular smokers willing to quit smoking.

This study is the first to combine approach bias retraining with VR techniques in the realm of addiction treatment. Still, over the last few years, VR approaches have made their ground in more traditional, mostly cognitive-behavioral interventions for psychiatric disorders. Mainly, VR-based techniques have become a promising effective and time-saving alternative for in vivo exposure-based therapy for specific phobias, including dental phobia [37], flight phobia [38], and spider phobia [39]. Moreover, VR has been used for neurocognitive assessments [40] and executive functioning training (for a review, see [41]). Although not used in CBM studies yet, an investigation by Schroeder and colleagues [42] revealed that a VR setting based on the AAT was capable of measuring an approach bias for palatable food in healthy subjects. Results derived from a related study [43] indicate that heavy social drinkers show difficulties in avoiding alcohol-related situations in a virtual environment, whereas no such difficulties were reported for light social drinkers. Hence, while research in this respect is still in its early stages, VR-based techniques hold promise in support of traditional health care.

VR bears several advantages over traditional computer-based techniques, which could offer a useful opportunity to improve the effectiveness of existing CBM programs. For example, VR enables the interaction with 3D-objects and allows for the implementation of complex scenarios that are hardly to provide using traditional PC-based interventions [44]. Thus, certain environments that fit a person’s everyday risk situations can be embedded into the VR-training, thereby narrowing the gap between laboratory trainings and actual real-life behavior. This approach, in turn, has merit in increasing training generalizability and efficacy. In addition, the deployment of more realistic environments can increase the enjoyment, motivation to train, and the feeling of immersion or presence. In turn, high levels of immersion, plausibly, will contribute to adherence and reduce dropout rates [45].

In summary, VR might offer an ecologically valid and promising approach to extend existing cognitive bias trainings, possibly augmenting the efficacy of current CM approaches.

